| Clinic Name | Screening Visits  # per year | African American  (%) | Hispanic  (%) | Under-insured  (%) | Low literacy  (%) | Spanish speaking  (%) |
| Ruskin | 33,800 | 5 | 50 | 85 | 40 | 30 |
| Plant City | 26,000 | 30 | 40 | 85 | 65 | 45 |
| Dover | 36,400 | 0 | 75 | 100 | 50 < 6th gr | 75 |
|  |  |  |  |  |  |  |
|  |  |  |  |  |  |  |
| Health Park | 20,800 | 40 | 20 | 70 | 40 | 5 |
| Midtown | 19,500 | 35 | 35 | 85 | 30 | 5 |

Since the start of the project, the number of participating clinics has increased (n=12) and they have been randomized as described below. Note that randomization occurred within sponsoring organization and for organizations with an odd number of clinics randomization was performed to insure that there were a greater number of intervention clinics than control.

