
**D.4 Phase II: To conduct a group randomized controlled trial to evaluate the Patient Navigator Program.**

### **D.4.1 Overview of Methods**

The goal of Phase II is to test whether a Patient Navigator Program implemented in the Tampa Bay region will lead to improved timeliness of cancer care, appropriateness of cancer care, and patient satisfaction. After careful consideration of several study designs for scientific rigor, feasibility, and acceptability by our community, we have selected a group randomized design (D.4.2), with the “group” being a community health center. The intervention arm will receive the Navigator Program first, and the control arm will receive the intervention, but delayed in time to permit the evaluation of program effectiveness. Patients within groups will be recruited by Clinical Research Assistants at the time of a suspicious screening result for cancer of the breast or colorectum (D.4.3). The Patient Navigators will assist the patients who have abnormal screening findings obtain timely appointments, referrals, and financial support that may be necessary. Data will be collected from medical records regarding timing of care and adherence of care to NCCN guidelines [82, 83] with chart abstractions occurring at 12 months, and patient satisfaction occurring for a randomly chosen subsample at baseline and again at 3 months. Data will be collected to assess, among other things, the patient’s navigation through, and satisfaction with, the health care delivery system (D.4.4).

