###### **D.4.3 Patient Recruitment**

As described previously, seven clinics will provide the Navigator Program and five clinics will not provide the Navigator Program based on random assignment. A description of the Navigator Program to be provided at those clinics randomized to this condition follows. We will make no attempt to alter the delivery of services at those clinics not randomized to deliver the Navigator Program. Rather, we will use both observational and survey methods to characterize the processes that typically occur in these clinics once patients are identified as having a breast or colorectal abnormality. These data will be used to characterize the extent to which delivery of care differed in our two intervention conditions.

The eligibility criteria were defined in D.2.1 above. Subjects having cancer-related abnormalities will be identified by research assistants using a variety of methods. Methodologies for identifying patients will be refined and pilot tested in the project’s first year. Procedures for subject identification and recruitment will be identical for intervention and control clinics. Once identified, patients will be contacted by research assistants for recruitment into the study. Research assistants will use the following sources to identify patients:

*Appointment records*: Appointment records provide the reason for each patient’s visit and will be assessed weekly by research assistants. This information will be used to identify cancer related symptoms (i.e. breast lumps, rectal bleeding).

*Screening logs*: Participating clinics maintain screening logs to document completion of cancer screening tests such as Pap smears, mammograms, and FOBT. Research assistants will track screening logs on a weekly basis to identify patients having abnormal results on mammography or FOBT.

*Referral coordinators*: Research assistants will also make at least weekly contact with referral coordinators at each clinic to identify patients who may have been referred for cancer related problems.

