**D.4.7.b Statistical Analysis and Study Power**

The statistical analyses will focus on those subjects receiving an abnormal or suspicious mammogram (BIRAD 0, 4, or 5) and those with abnormal FOBTs or abnormalities detected on sigmoidoscopy (see D.2.1). Those in the Navigator intervention groups will be compared to those in the control groups with respect to two outcomes. For patients with breast or colorectal abnormalities, the primary outcome will be time from detection of abnormality to definitive diagnosis, measured as a continuous variable. In addition, we will assess the proportion of patients who successfully complete an appropriate diagnostic evaluation. The records of each subject with such an indication for follow-up will be examined as described in D.3.3.

Study power is based on the following factors. The primary endpoint is ‘Length of time’ (LOT=time from screening to definitive diagnosis). Suppose LOT follows a normal distribution (mean=30 days, “std” = standard deviation). Then, to detect the difference in LOT between two groups (navigator versus control groups), a two-sample t-test will be used. The required minimum sample size to achieve 80% statistical power is calculated based on the t-test and illustrated in Figure 1.

For example, group sample sizes of 29 and 29 (total 58) achieve 80% power to detect a difference of 10 days between the null hypothesis that both group means are 30.0 and the alternative hypothesis that the mean of Navigator group is 20 days with estimated group standard deviations of 15.0 each and with a significance level of 0.05 using a one-sided two-sample t-test. However, to detect a difference of 5 days with the same standard deviation 15.0 between the two groups, one would need at least 112 samples for each group (total 224).

Figure 1. Required sample sizes for each group based on the expected mean of navigator group by the standard deviation. For the control group, the mean value of LOT was set up as 30.0. The standard deviations for both groups are assumed to be equal. α=0.05 (one sided: mean 1 > mean 2).

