Although we do not expect attrition of clinics, we have assessed power the possibility of between 6 and 8 participating clinics enrolling about 100 subjects each (a total of 600 - 800 subjects). Depending on the intracluster correlation coefficient (ICC) and the design effect, however, there may be effectively fewer subjects enrolled in this study from a statistical perspective. Assuming the intracluster correlation coefficient (ICC) to be in the range of 0.01 through 0.04, the effective sample sizes will be obtained as follows,

| # of total clinics | Actual Sample Sizes | ICC | Design Effect | Effected Sample Sizes |
| --- | --- | --- | --- | --- |
| 8 | 800 | 0.01 | 1.99 | 402 |
| 6 | 600 | 0.01 | 1.99 | 302 |
| 8 | 800 | 0.02 | 2.98 | 268 |
| 6 | 600 | 0.02 | 2.98 | 201 |
| 8 | 800 | 0.04 | 4.96 | 161 |
| 6 | 600 | 0.04 | 4.96 | 121 |

Therefore, given our expected sample sizes (600-800 subjects) even under the most conservative conditions (low design effects or ICC values, and relatively high population standard deviation), we will expect the desired statistical power will be achieved.

We will also conduct a number of secondary analyses in an exploratory fashion. For those with a suspicious screening result, we will compute the Kaplan-Meier curves for time from the suspicious result to definitive diagnosis (positive or negative) for each randomized arm. For those with positive diagnoses, we will compute Kaplan-Meier curves for time to onset of therapy for each randomized arm from both suspicious screening result and definitive diagnosis. In each case, we will estimate the standard error of these estimates with Greenwood’s formula and produce 95% confidence bands for these curves using the method of Hall and Wellner. The log rank test will be used to compare the two randomized groups. These comparisons will be at the two-sided 0.05 significance level.

Degree of adherence to NCCN standards will be assessed by an independent assessor blinded with respect to randomized arm and rated as 1 = complete adherence, 2 = substantial adherence, or 3 = poor adherence. The two randomized arms will be compared with respect to these adherence ratings using Wilcoxon’s Rank Sum Test.

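### Clinics are randomised, but the only primary test named is a patient-level t-test that ignores clinic, so its one-sided error exceeds the nominal 5%

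*Protocol*

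**What the plan says.** Protocol D.4.1 makes the clinic the unit of randomisation: "we have selected a group randomized design (D.4.2), with the “group” being a community health center". Section D.2 updates the number: "Since the start of the project, the number of participating clinics has increased (n=12) and they have been randomized as described below", and adds: "Note that randomization occurred within sponsoring organization". The lists that follow show five organisations, with navigator and control clinics split 1:1, 2:1, 1:1, 2:1 and 1:1. Section D.4.3 gives the total: "seven clinics will provide the Navigator Program and five clinics will not provide the Navigator Program based on random assignment".

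Section D.4.7.b takes time to definitive diagnosis as a continuous primary outcome and says of the test: "Then, to detect the difference in LOT between two groups (navigator versus control groups), a two-sample t-test will be used". Its worked example is one-sided at 0.05. The same section then assumes an intracluster correlation (ICC) of 0.01 to 0.04 with about 100 subjects per clinic, and reduces 600-800 subjects to an effective 121-402.

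Among the secondary analyses are Kaplan-Meier curves with Greenwood standard errors and Hall-Wellner bands. For these, "The log rank test will be used to compare the two randomized groups", at two-sided 0.05. On guideline adherence, "The two randomized arms will be compared with respect to these adherence ratings" by Wilcoxon's rank-sum test. No mixed model, estimating equation, robust variance, clinic-level summary or cluster degrees of freedom appears anywhere in the Protocol.

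**The concern.** A two-sample t-test on patients takes its standard error from the number of patients. When clinics are randomised, the difference between arms also carries clinic-to-clinic variation, and only 12 clinics average it out. The plan accepts this when it counts 800 patients as 161 for power, but its named test would count all 800 for inference. The standard error is then too small by the square root of the design effect, a factor of 1.41 to 2.23 on the plan's own figures.

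The risk is that a programme with no effect is declared effective. The primary result feeds the dissemination plan (D.5.1), and statistically significant differences serve as denominators in the cost-effectiveness ratios described in D.4.7.c, so a false positive would carry forward.

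**Working it through.** **Inputs (Protocol).** SD 15 days, differences of 10 and 5 days, one-sided 0.05, 80% power, ICC 0.01-0.04 and about 100 per clinic (D.4.7.b); 12 clinics, 7 v 5 (D.2, D.4.3); at most 1600 in Phase II (E.1.1).

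**Step 1: the plan's own figures.** n per group = 2 × (1.645 + 0.842)² × 15² / difference².
- 10 days: 27.8 by the normal formula and 28.5 by the exact t-test, so 29, as stated.
- 5 days: 111.3 and 111.97, so 112, as stated.
- Two-sided versions (36-37 and 142-143) do not match, so the stated primary calculation is one-sided.
- Design effect DE = 1 + (m − 1) × ICC with m = 100 gives 1.99, 2.98 and 4.96. Then 800/DE = 402, 268, 161 and 600/DE = 302, 201, 121. All six rows reproduce.

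**Step 2: true error of the unadjusted test.** If the real variance is DE times what the test assumes, the one-sided error is 1 − Φ(1.645/√DE). For m = 100 and ICC 0.04, 1.645/√4.96 = 0.739, which gives 23.0%.

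| Patients per clinic | DE at ICC 0.01 / 0.02 / 0.04 | True one-sided error |
|---|---|---|
| 50 (600/12) | 1.49 / 1.98 / 2.96 | 8.9 / 12.1 / 17.0% |
| 67 (800/12) | 1.66 / 2.32 / 3.64 | 10.1 / 14.0 / 19.4% |
| 100 (plan's figure) | 1.99 / 2.98 / 4.96 | 12.2 / 17.0 / 23.0% |
| 133 (1600/12) | 2.32 / 3.64 / 6.28 | 14.0 / 19.4 / 25.6% |

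Simulation with 7 v 5 clinics of 100 (40,000 replicates) gave 12.6, 17.1 and 23.3%. A t-test on the 12 clinic means in the same runs held 5.1-5.3%.

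**Step 3: randomisation within organisation.** Variation shared by clinics of one organisation partly cancels between arms. The Protocol does not say how much is shared, so this is an assumption. Simulation at 100 per clinic for ICC 0.01 / 0.02 / 0.04 gave:
- none shared: 12.4 / 17.2 / 22.9%
- half shared: 9.3 / 12.3 / 17.4%
- 80% shared: 7.0 / 9.3 / 12.2%

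**Step 4: secondary analyses.** The two-sided counterpart is 2 × [1 − Φ(1.96/√DE)]. For the log-rank test on all patients with a suspicious result, assuming a similar ICC and 100 per clinic, it gives roughly 16, 26 and 38%. Time to therapy is confined to diagnosed cancers, and adherence in practice probably is too. With an assumed 5 to 20 cancers per clinic, DE runs from 1.04 to 1.76 and the error from about 5.5% to 14%.

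**The case against.** The t-test sentence stands in the paragraph that derives the sample size. The analysis paragraph before it names the outcome but no test. The authors plainly knew about clustering, and details such as random effects and degrees of freedom are often left to a statistical analysis plan, which may exist. This lowers certainty that an unadjusted t-test would in fact be run. It does not remove the point: the section is headed as analysis as well as power, it says the test will be used, and no other primary test is named. A stated test that does not fit the design is different from a detail left for later.

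The objection on size also has force. The 100 per clinic comes from a scenario of 6-8 clinics. The same 600-800 patients over 12 clinics is 50-67 each. The 1600 is a ceiling, and D.4.7.b focuses the analysis on a narrower set of abnormalities than D.2.1 admits. Smaller clusters mean less inflation, as does variance shared within organisations.

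A reader might infer that every listed analysis has a false-positive rate several times 5%, or that the primary rate reaches 38% or more. The documents do not support either. Greenwood's formula gives a standard error, so the consequence is bands that are too narrow. The Kaplan-Meier and log-rank analyses are labelled exploratory. Cancer-only comparisons have small clusters. The two-sided figures do not describe the one-sided primary test.

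**Conclusion.** The point holds for the primary analysis as written. Its one-sided error is about 2.4 to 4.6 times nominal at 100 patients per clinic and about 1.8 to 3.9 times at 50-67 per clinic. These figures rest on the plan's ICC range, equal clinic sizes and no variance shared within organisations. With half to 80% shared, the error at 100 per clinic is about 7-17%. It stayed above 5% in every case examined.

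For the secondary analyses, the conclusion is only that they omit clustering in the same way. The effect is material for the log-rank comparison of all patients and smaller for those confined to diagnosed cancers.

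**What to change.** Name a primary analysis at the level randomised, and state that it replaces the t-test. Either of these would do:

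- a patient-level model with a random clinic effect and small-sample degrees of freedom: 12 − 2 = 10, or 12 − 6 = 6 if the five organisations are also fitted;
- a permutation test over the allocations possible within organisations: 2 × 3 × 2 × 3 × 2 = 72. The smallest p-value is 1/72 = 0.014, and the attainable one-sided level is 3/72 = 0.042. The plan should confirm that these allocations were equally likely.

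Use clinic-robust, frailty or permutation versions for the log-rank and Wilcoxon comparisons, and cluster-adjusted standard errors and bands for the Kaplan-Meier curves.

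The cost is protocol wording and a different SAS procedure, with no extra data. Stated precision becomes less favourable. With 7 v 5 clinics of 100, a one-sided clinic-level t-test (10 df) has power of 98, 92 and 77% for 5 days at ICC 0.01, 0.02 and 0.04, and at least 99% for 10 days. Power is lower with fewer patients per clinic, so it should be restated for the 12 clinics and the expected enrolment.

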Insurance payer category was significantly associated with stage at diagnosis for each of the four cancer sites examined. Patients insured by Medicaid and those who were uninsured were at greater risk for late-stage disease. Non-Hispanic blacks were at greater risk of late stage diagnosis for breast and prostate cancers. Two payer categories were found to have significantly greater odds of late-stage colorectal cancer than the referent category of commercial indemnity insurance: Medicare HMO and uninsured. Patients who were non-Hispanic black or Hispanic were more likely diagnosed at a late stage independent of their insurance payer. There was a non-significant trend for patients of "other" race-ethnicity to have a more favorable stage at diagnosis. A plausible explanation for a later stage at diagnosis among the uninsured is inadequate access to cancer screening services. Persons lacking health insurance are less likely to receive cancer screening and other preventive services, [17, 57, 58] and may have delayed diagnosis of symptomatic cancers due to inadequate access to health care.

These data motivated [name] and colleagues to conduct the Cancer SOS project, a four-year cluster-randomized trial of an office systems intervention designed to increase cancer screening in primary care clinics that provide care to underserved populations[45]. Eight clinics were recruited from among community health centers in Hillsborough County, Florida. The study targeted men and women between the ages of 50 and 75 and focused on three cancer screening tests that are widely recommended for this age group. For women, the materials and methods were intended to increase the use of mammograms, Pap smears, and fecal occult blood testing (FOBT). For men, the materials and methods were intended to increase the use of FOBT.

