**Suncoast Community Health Centers**

Ruskin Health Center Intervention

Plant City Family Care Intervention

Dover Health Center Control

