| Physician referrals (type, dates referred, dates completed) | *Clinic record* |
| Date definitive diagnosis given to abnormality | *Clinic record, outside records* |
| **Clinical data on cancer diagnosis and treatment** | **Data Source** |
| Type of cancer, AJCC Stage at diagnosis | *Clinic record, outside records* |
| Treatments initially recommended | *Clinic record, outside records* |
| Referrals for treatment (type, dates referred, dates referral completed) | *Clinic record, outside records* |
| Cancer directed surgery (type, dates) | *Clinic record, outside records* |
| Cancer directed radiation therapy (type, dates initiated, dates completed) | *Clinic record, outside records* |
| Cancer directed chemotherapy (type, dates initiated, dates completed) | *Clinic record, outside records* |
| Cancer directed hormonal therapy (type, dates initiated) | *Clinic record, outside records* |
| Palliative / supportive therapies (types, dates initiated) | *Clinic record, outside records* |
| Hospitalizations (dates, length of stay) | *Clinic record, outside records* |
| Vital status / *Date of death (if applicable)* | *Clinic record, outside records* |

| **Other relevant patient medical information** | **Data Source** |
| --- | --- |
| Patient age, gender, race-ethnicity, marital status | Clinic record, Intake interview |
| Patient employment | Clinic record, Intake interview |
| Patient educational attainment | Intake interview |
| Type of residence (home, apartment) | Intake interview |
| Who else lives with patient | Intake interview |
| Health insurance type | Clinic record, intake interview |
| Family history of breast or colorectal cancer | Clinic record |
| Estrogen replacement therapy | Clinic record |
| History of benign breast disease (previous biopsies) | Clinic record |
| Comorbidity (Charlson Comorbidity Index) | Clinic record |
| Number of health care visits since index visit | Clinic record |
| Previous mammograms (dates, results) | Clinic record |
| Previous clinical breast examinations (dates, results) | Clinic record |
| Previous colorectal cancer screening tests (types, dates, results) | Clinic record |

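### The only test named for the primary outcome is an unadjusted t-test, although the known allocation of 7 v 5 clinics can leave insurance and language unbalanced, as the Suncoast clinics show

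*Protocol*

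**What the plan says.** Protocol D.4.7.b makes time from abnormality to definitive diagnosis the primary outcome, measured as a continuous variable. For the arm comparison it says that "to detect the difference in LOT between two groups (navigator versus control groups), a two-sample t-test will be used". The worked example is run "with a significance level of 0.05 using a one-sided two-sample t-test". No other test is named for this outcome as a continuous measure. The exploratory log-rank comparison of the same interval and the Wilcoxon test for guideline adherence are also described without covariates. Clustering appears only as a design effect that shrinks the sample size in the power discussion.

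D.2 reports that 12 clinics have been randomised within sponsoring organisation and lists each clinic's arm. D.4.3 confirms seven intervention and five control. Table D.2 profiles five clinics. One row reads "Dover | 36,400 | 0 | 75 | 100 | 50 < 6th gr | 75", where the last three entries are under-insured, low literacy and Spanish-speaking. The allocation list gives "Dover Health Center Control".

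On why these characteristics matter:
- C.2 says that people without insurance "may have delayed diagnosis of symptomatic cancers due to inadequate access to health care".
- B.1 names English proficiency among the variables that affect access to care.
- D.4.4 has navigators look for barriers to timely services, insurance funding among them.

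The variable table in D.3.3.1 includes "Health insurance type | Clinic record, intake interview".

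**The concern.** With 12 clinics, randomisation cannot be relied on to balance patient mix, and here the result of the draw is already visible for some of them. At Suncoast the single control clinic has the highest under-insured and Spanish-speaking shares in Table D.2. If such patients wait longer for a diagnosis whatever the arm, part of the difference at Suncoast would reflect who attends Dover. An unadjusted comparison cannot separate that from the effect of navigation. Randomising within organisation does not help, and nor would a term for organisation, because the gap lies inside one organisation. Where the control arm holds more such patients, the error favours navigation; where it holds fewer, the error hides a benefit.

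**Working it through.** **1. The plan's own figures.** Inputs from D.4.7.b: one-sided 0.05, 80% power ("The required minimum sample size to achieve 80% statistical power is calculated based on the t-test"), and for the first example "the mean of Navigator group is 20 days with estimated group standard deviations of 15.0 each" against 30 days in control.
- Normal approximation: n per group = 2(1.645 + 0.842)² × 15² / d². This gives 27.8, so 28, for d = 10, and 111.3, so 112, for d = 5.
- Exact t: 29 per group gives power 0.806 (28 gives 0.793), and 112 gives 0.800.

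The stated 29 and 112 are reproduced. They are sample sizes for an unadjusted one-sided t-test.

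**2. Profiles matched by name** (Table D.2 against the allocation list in D.2):

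| Clinic | Arm | Under-insured % | Spanish-speaking % | Low literacy % |
|---|---|---|---|---|
| Ruskin | Intervention | 85 | 30 | 40 |
| Plant City | Intervention | 85 | 45 | 65 |
| Health Park | Intervention | 70 | 5 | 40 |
| Dover | Control | 100 | 75 | 50 (below 6th grade) |

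Within Suncoast, taking the simple mean of the two intervention clinics:
- under-insured (85 + 85)/2 = 85% v 100%, a gap of 15 points;
- Spanish-speaking (30 + 45)/2 = 37.5% v 75%, a gap of 37.5 points.

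The fifth profile, Midtown (85% under-insured, 5% Spanish-speaking), is not in the allocation list. Tampa General's control clinic, Kennedy, has no profile under that name. If the two are the same clinic (assumption), the Tampa General pair is 70% v 85% under-insured and 5% v 5% Spanish-speaking.

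**3. What is known trial-wide.** Four of seven intervention clinics and four of five control clinics have no name-matched profile. Let each of these lie anywhere from 0 to 100%, and take control minus intervention in clinic means:
- under-insured: lowest 100/5 − (240 + 400)/7 = −71 points; highest 500/5 − 240/7 = +66 points;
- Spanish-speaking: lowest 75/5 − (80 + 400)/7 = −54 points; highest 475/5 − 80/7 = +84 points.

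The sign is not determined.

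**4. A less extreme illustration.** Assume that Midtown is Kennedy and that the other seven clinics (four intervention, three control) are all 85% under-insured:
- control (100 + 85 + 3 × 85)/5 = 88.0%;
- intervention (85 + 85 + 70 + 4 × 85)/7 = 82.9%;
- gap 5.1 points.

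For any common rate from 0 to 100% in those seven clinics the gap is 2.7 to 5.6 points. Without the Midtown assumption, a common rate v in the eight unmatched clinics gives (100 + 4v)/5 − (240 + 4v)/7. That is −2.9 points at v = 50 and +5.1 points at v = 85.

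**5. What 5.1 points could do to the test.** The protocol gives no delay in days by insurance status, so the delays below are assumptions. Assume also 100 patients per clinic (700 v 500), SD 15 and no true effect. SE = 15 × √(1/700 + 1/500) = 0.878 days. Shift = 0.0514 × delay. False-positive rate = 1 − Φ(1.645 − shift/SE).

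| Assumed extra wait if under-insured | Shift favouring navigation | One-sided false-positive rate (nominal 5%) |
|---|---|---|
| 5 days | 0.26 days | 9% |
| 10 days | 0.51 days | 14% |
| 20 days | 1.03 days | 32% |

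These rates leave out clustering, which is a separate problem for the same test.

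**The case against.** The strongest reply is that an arm-level imbalance has not been shown. That stands: only one control clinic is matched by name. A reader might infer that the control arm as a whole holds the patients expected to wait longest, and that the trial is therefore biased towards navigation. The documents do not support this, for four reasons.
- Eight of 12 clinics are unprofiled by name.
- Other columns lean the opposite way. With Midtown counted as control, mean low literacy is 48.3% in intervention and 40% in control, and mean African American share is 25% v 17.5%.
- Table D.2 describes clinic populations, not enrolled patients. D.4.6b expects providers to refer patients with more barriers to navigation, which would pull towards the null.
- The links to delay are limited. C.2 speaks of people lacking insurance rather than the under-insured, and B.1.1 ties language to screening use.

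It can also be said that chance imbalance does not by itself invalidate a randomised comparison, that the t-test sentence sits in the power text, and that covariates are often left to a statistical analysis plan. The first is true of the procedure averaged over all possible allocations, but here the allocation is known and part of its imbalance can be seen. On the other two, the protocol does state a test, and that test has no adjustment. An unknown sign is also a reason to adjust, since patient-level adjustment for these two factors works in either direction.

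Patient language is not an itemised variable in the protocol, so it has to come from a proxy. That is a real limit on the remedy.

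**Conclusion.** The point holds in a limited form. The named primary comparison is unadjusted. The known allocation contains a clear imbalance at Suncoast: 85% v 100% under-insured and 37.5% v 75% Spanish-speaking. These are factors that the protocol itself connects with poor access or delay, so a difference they produce could be credited to navigation, and a term for organisation would leave it in place. The net direction and size over all 12 clinics cannot be determined from the protocol. The gap of about 5 points and the 9%, 14% and 32% error rates depend on the identity of Midtown, a common 85% rate elsewhere, 100 patients per clinic and assumed delays. They show what could happen and are not estimates of bias in this trial. The case for changing the plan is that the remedy is cheap, works in either direction and fixes the covariates before results are seen.

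**What to change.** In D.4.7.b, take the primary estimate from a model for time to definitive diagnosis that:
- adjusts for insurance status at enrolment, before navigation starts, because D.4.4 has navigators help patients secure benefits and a later value could be affected by the intervention;
- adjusts for language, English v Spanish, taken from which literacy instrument was used at baseline (REALM or SAHLSA, administered in both arms under D.4.5);
- includes sponsoring organisation, within which clinics were randomised;
- accounts for clustering by clinic.

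Keep the unadjusted comparison as supportive, tabulate both covariates by arm, and use a missing category for unknown insurance.

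The cost is analysis wording and slightly more analysis work. Insurance type is already listed as a clinic-record and intake item in D.3.3.1. The drawback is that language is measured by proxy.
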